## Abstract

**Background:**

Because of high demands at work, nurses are at high risk for occupational burnout and physical complaints. The presence of job resources (such as job autonomy or social support) and recovery opportunities could counteract the adverse effect of high job demands. However, it is still unclear how job resources and recovery opportunities can be translated into effective workplace interventions aiming to improve employee health, well-being, and performance-related outcomes. The aim of the current research project is developing and implementing interventions to optimize job resources and recovery opportunities, which may lead to improved health, well-being and performance of nurses.

**Methods/design:**

The DIRECT-project (DIsc Risk Evaluating Controlled Trial) is a longitudinal, quasi-experimental field study. Nursing home staff of 4 intervention wards and 4 comparison wards will be involved. Based on the results of a base-line survey, interventions will be implemented to optimize job resources and recovery opportunities. After 12 and 24 month the effect of the interventions will be investigated with follow-up surveys. Additionally, a process evaluation will be conducted to map factors that either stimulated or hindered successful implementation as well as the effectiveness of the interventions.

**Discussion:**

The DIRECT-project fulfils a strong need for intervention research in the field of work, stress, performance, and health. The results could reveal (1) how interventions can be tailored to optimize job resources and recovery opportunities, in order to counteract job demands, and (2) what the effects of these interventions will be on health, well-being, and performance of nursing staff.

## Background

Nurses are at high risk for occupational burnout [1-3] and physical complaints, merely due to high demands at work [4,5]. Because job demands often cannot be easily reduced, it is rather appealing to counteract the adverse effects of high job demands on well-being and health with so-called job resources [6]. Job resources can be broadly conceptualized as different kinds of energey reservoirs that can be tapped when the employee has to cope with job demands [7,8]. Examples of job resources are job autonomy, colleagues providing help, sympathy, and affection, and ergonomic aids. Empirical research has shown that job resources are important stress buffers for nurses [9]. In addition, Taris et al. [10] showed that a well-balanced mix of job demands and job resources is positive related to well-being, and that well-being is positive related to performance indicators such as client satisfaction and efficiency.

Besides the availability of job resources to counteract high job demands, recovery from job demands can also be an important prerequisite for not feeling strained and for performing well when returning to work the next day. According to Meijman and Mulder [11], recovery occurs when no further demands are put on those aspects of an individual's functioning on which job demands have been put during the work process. There is empirical evidence showing that recovery from work is positively related to employees' health and well-being [12-15], as well as to job performance [16].

Because job demands can often not be reduced, organizations need to implement workplace interventions that revolve around the management of job resources and recovery opportunities. However, there is a gap between theoretical knowledge gained from work stress and performance models and their practical implications [17]. According to Kompier and Taris [18], there is a strong need for intervention research in the field of work, stress, performance, and health. The current research project fills-in this gap by developing and implementing interventions to optimize job resources and recovery opportunities. This may lead to improved health and performance of nurses. Because a systematic analysis of risk factors is often lacking in stress intervention research [19], a strength of the present study is the adequate diagnosis of risk factors conform a recent developed theoretical model called the Demand-Induced Strain Compensation (DISC) Model [6,20]. This is in line with Goldenhar et al. [21], who called for *theory-driven *intervention research to learn why and under what circumstances work-oriented interventions succeed.

In more detail, the DISC Model treats job demands and job resources as multidimensional constructs. In line with Hockey [22], three type of job demands can be distinguished: (1) cognitive demands which primarily impinge on the brain processes involved in information processing [22], (2) emotional demands which primarily refer to the effort needed to deal with organizationally desired emotions during interpersonal transactions [23], and (3) physical demands which are primarily associated with the musculo-skeletal system [22]. Similarly, job resources may encompass a cognitive component (e.g. access to useful information from books), an emotional component (e.g. colleagues providing sympathy and affection), and a physical component (e.g. ergonomic aids). Finally, in line with Sonnentag and Niessen [24], recovery from work can also be divided in a cognitive component (think on other things than work), an emotional component (put all emotions from work aside), and a physical component (i.e. not longer affected by the work posture). Based upon homeostatic functional self-regulation processes, the DISC Model proposes that job resources as well as recovery within the same domain as the job demands (i.e. cognitive, emotional, or physical) will produce a greater likelihood of counteracting the negative job demands and creates optimal conditions for health, well-being, and performance [25]. For example, high emotional job demands (e.g. dealing with dying patients) can lead to emotional exhaustion, unless employees have high emotional resources (e.g. social support from colleagues) and a high level of emotional recovery (e.g. meeting with friends after work) to counteract the high emotional demands.

### Aim and research question

The aim of the current study is developing, implementing, and evaluating interventions to optimize job resources and recovery opportunities, which may lead to improved health, well-being and performance of nurses. The interventions that will be implemented after a baseline measure, will be based on the central principle of the DISC Model, i.e. the amount of specific job resources and recovery opportunities have to match with the corresponding types of job demands to optimize job-related outcomes. These interventions will be primarily work-oriented, i.e. changing the work situation rather than changing the employee or his/her perceptions. A meta-analysis of stress management interventions [26] showed that only a few studies assessed the impact of work-oriented interventions, and that there is a paucity of research which compared different kinds of interventions on respective, similar, outcomes. The research question is: Does a tailored intervention program based upon the DISC Model result in an improvement of employee health, well-being and performance-related outcomes? In other words, how can job demands, job resources, and recovery both during and after work time be optimized to improve health, well-being and performance of nursing staff?

## Methods and design

### Overview

The DIRECT-project (DIsc Risk Evaluating Controlled Trial) is a longitudinal, quasi-experimental field study (February 2009-February 2011) with a 'non-equivalent control group pretest posttest design' [27]. Employees within two Dutch nursing homes will participate in the research project, one in the North of the Netherlands and one in the South. In the nursing home in the North of the Netherlands two wards on one location will be the intervention group and two wards on another location will be the comparison group. In the Southern nursing home two wards will be the intervention group and two wards in the same location will be the comparison group. In total, four wards will be the intervention group (*n *= 150) and four wards will be the comparison group (*n *= 150). The more realistic terminology 'comparison group' was selected explicitly in contrast to 'control group' as the formal requirements for a real control group are not met [28]. Figure 1 presents a flow-chart of the design and measurements. Based on the result of the base-line survey (T1), workplace interventions will be implemented to optimize job demands, job resources, and recovery both during and after work time. One year after the baseline measurement, the results of the interventions will be evaluated by a follow-up survey (T2). To investigate if the interventions lead to enduring higher performance, well-being and employee health, a second follow-up survey will be conducted two year after the base-line measure (T3). In addition to the follow-up surveys, which will measure the effect of the interventions, a process evaluation will be performed.

**Figure 1 F1:**
[figure not shown]
**Flow chart design and measurements**.

### Participants

All nursing staff (i.e. nursing assistants, certified nursing assistants, and registered nurses) working on a permanent basis at one of the eight wards, will be eligible to participate in the study. Because of the longitudinal character of the project, temporary staff will be excluded.

### Measures

The measures that will be used in both the baseline survey and the follow-up surveys are described below.

### DISC-Model measures

*Cognitive, emotional and physical job demands and job resources *will be measured with a well-validated version of the DISC Questionnaire (DISQ), which was particularly developed for testing this theoretical model [9,29]. *Cognitive job demands *primarily impinge on brain processes involved in information processing, e.g., "Employee X will need to display high levels of concentration and precision at work". *Emotional job demands *can be defined as the effort needed to deal with job inherent emotions and/or organizationally desired emotions during interpersonal transactions, e.g., "Employee X will have to display emotions (e.g., towards clients, colleagues or supervisors) that are inconsistent with his/her current feelings". *Physical job demands *refer to static and dynamic physical exertion at work, e.g., "Employee X will have to lift or move heavy persons or objects (more than 10 kg)". *Cognitive job resources *refer to the opportunity to determine a variety of task aspects and to use problem solving skills, e.g., "Employee X would have the opportunity to take a break when tasks require a lot of concentration". To improve the internal reliability of the scale, one item was added to the original questionnaire ("Employee X will have the opportunity to determine their own work method"). *Emotional job resources *refer to emotional support from colleagues or supervisors, e.g., "Other people (e.g., clients, colleagues or supervisors) would be a listening ear for employee X when he/she has faced a threatening situation". Finally, *physical job resources *refer to instrumental support from colleagues and supervisors, or ergonomic aids at work, e.g., "Employee X would receive help from others (e.g., clients, colleagues or supervisors) in lifting or moving heavy persons or objects". All but two scales consist of five items (except for emotional demands and cognitive resources: six items) that can be scored on a 5-point frequency scale, ranging from 1 *(never or very rarely) *to 5 *(very often or always) Recovery from work*. Recovery refers to an employee's sense of being away from the work situation. It will be measured with a scale developed by De Jonge et. al. ("Take a break?" Off-job recovery, job demands and job resources as predictors of active learning, creativity, and health, submitted) and may encompass a cognitive, emotional and physical component. Each component will be measured with three items. Example items are: "After work, I put all thoughts of work aside" (cognitive), "After work, I emotionally distance myself from work" (emotional), "After work, I shake off the physical exertion from work" (physical). The items can be scored on a 5-point frequency scale, ranging from 1 *(never) *to 5 *(always)*.

### Health measures

*Concentration problems *will be measured with three items derived from a semantic differential scale developed by Meijman [30]. The 5-point response scale have two extremes, for example *'No concentrating difficulties' *and *'Concentration difficulties'. Emotional exhaustion *will be measured by the well-validated Dutch version [31] of the Maslach Burnout Inventory [32]. The scale contained five items with a 7-point response scale ranging from 0 *(never) *to 6 *(always, daily)*. An example item is: "I feel emotionally drained from my work".

*Physical complaints *refer to neck, shoulder and back problems in the last six months and will be measured with three items derived from a scale developed by Hildebrandt and Douwes [33]. The possible responses are 1 *(no)*, 2 *(sometimes)*, and 3 *(yes)*.

### Well-being measures

*Job satisfaction & Work motivation *will be measured by scales developed by De Jonge [34]. Job satisfaction can be considered as a unidimensional and general construct, resulting from positive and negative work experiences. It will me measured with one item i.e. "I am satisfied with my present job". Work motivation is the extent to which the work is stimulating, interesting, and challenging and will be measured with five items. For example, "My work is very interesting". All items are measured on a 5-point Likert scale, ranging from 1 *(strongly disagree) *to 5 *(strongly agree)*.

### Performance measures

*Active learning *refers to the degree employees are enabled and stimulated to acquire new knowledge and skills, and to solve problems at their job. This scale [35] consists of four items that can be scored on a 4-point frequency scale, ranging from 1 (*(almost) never*) to 4 (*(nearly) always*). For example, "At work, I am challenged by new problems".

*Employee creativity *can be defined as the generation of novel and useful ideas by employees. This work-related construct will be assessed by a 7-item scale originally developed by George and Zhou [36], and translated/back-translated in a well-validated Dutch version [37]. The scale can be scored on a 5-point rating scale ranging from 1 (*never*) to 5 (*always*). For example "Comes up with new and practical ideas to improve performance".

### Development of workplace interventions

Based on the results of the base-line survey the researchers will develop risk-profiles for each ward, which report the specific job demands, job resources, and recovery opportunities of the wards involved. Figure 2 presents an example of a risk-profile. It shows that particularly physical job resources and physical recovery are rather low to counteract the amount of physical job demands. The risk-profiles will be the starting-point for the researchers to generate ideas for workplace interventions that could be implemented to optimize job resources and recovery opportunities on the intervention wards. For developing and implementing interventions, a Participatory Action Research (PAR) approach will be used [38]. The philosophy behind PAR is that interventions designed to improve job-related outcomes cannot take place without the participation and experience of the subjects under study. The effectiveness of PAR in intervention research has been demonstrated empirically [39-41]. How will PAR be used in the present study? The results of the base-line survey together with the ideas for possible interventions from the researchers, will be discussed in small groups of employees from the experimental wards (i.e. intervention mapping). After consensus about interventions with the highest priority, employees will be made self-responsible for the implementation of (a part of) the interventions. During the process of developing and implementing interventions the researchers will be supported by an external consultant. How will the interventions look like? Figure 2 showed for example that the availability of physical job resources and physical recovery opportunities for this ward are rather low to counteract the relatively high physical job demands. To enlarge the amount of physical resources it can be important to check if there is sufficient adequate technical equipment to accomplish physically strenuous tasks and if this equipment is used correctly by the employees. Physical recovery at/after work can for example be improved by establishing fitness programmes or other sport and physical activities. To conclude, the ward-profiles will serve as the basis for the development of tailored ward-directed interventions. Figure 3 showed examples of workplace interventions based upon different kinds of job resources and recovery at/after work. All the interventions that will be implemented are primarily work-oriented rather than worker-oriented.

**Figure 2 F2:**
[figure not shown]
**Example of a risk-profile**.

**Figure 3 F3:**
[figure not shown]
**Examples of work-oriented interventions based upon different kinds of job resources and recovery at/after work**.

### Evaluating the effects of workplace interventions

After the implementation of workplace interventions and the first follow-up survey, a change-profile will we developed for each ward. The change-profile from a ward is exactly the same as the risk-profile but contains also the scores on specific job demands, job resources, and recovery opportunities from the follow-up survey. Figure 4 shows an example of a change-profile, indicating a positive effect on physical job resources and physical recovery. Because job demands are difficult to change, these scores are almost equal as the scores from the base-line survey. However, the amount of physical job resources and physical recovery opportunities for this ward are increased, so the employees will be better able to counteract their relatively high physical job demands. The increase in specific job resources and recovery opportunities is called the change-area. The change-profile shows if an intervention is successful in increasing specific types of job resources and recovery opportunities. However, to determine the effect on an outcome measure (e.g. physical complaints), the average score of the first follow-up survey will be compared with the score from the base-line survey. To investigate the enduring effects of the interventions, change-profiles will be developed again after the second follow-up survey.

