#### Data-analysis

Cross-sectional, baseline, relations between specific types of job demands, job resources, recovery and job-related outcomes will be tested with hierarchical regression analysis (SPSS for Windows) and structural equation modeling (LISREL for Windows). In order to analyze causal associations within the two different waves, structural equation modeling (LISREL for Windows) will be used, as this technique is more useful to 'prove' causation (i.e. to rule out alternative, causal, assumptions). To evaluate the results of the interventions after the follow-up measures, multilevel repeated measures analysis will be performed using MLwiN. This technique has several advantages compared to repeated measures MANOVA, like the inclusion of cases with incomplete data and less restrictive missing data assumptions.

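### The ward change-profile is said to show intervention success, but no minimum change, interval or comparison-ward contrast is attached and the reading is not tied to the planned multilevel model

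*Protocol article*

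**What the plan says.** The section on evaluating the effects of workplace interventions defines the display: "The change-profile from a ward is exactly the same as the risk-profile but contains also the scores on specific job demands, job resources, and recovery". The added scores are those collected at follow-up. It then names the difference: "The increase in specific job resources and recovery opportunities is called the change-area". It attaches a conclusion to that difference: "The change-profile shows if an intervention is successful in increasing specific types of job resources and recovery opportunities". The profiles are to be drawn up again after the second follow-up.

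The worked example in the same section says of job demands: "Because job demands are difficult to change, these scores are almost equal as the scores from the base-line survey". Outcome measures are handled in a separate sentence, under which "the average score of the first follow-up survey will be compared with the score from the base-line survey".

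The underlying risk-profiles, described under Development of workplace interventions, report "the specific job demands, job resources, and recovery opportunities of the wards involved". Under Measures, job resources and recovery each have a cognitive, an emotional and a physical component, scored from 1 to 5.

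The formal analysis is in a different section, Data-analysis: "To evaluate the results of the interventions after the follow-up measures, multilevel repeated measures analysis will be performed using MLwiN". That sentence does not mention the change-profile, and the change-profile paragraph does not mention the model.

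**The concern.** The change-profile, as described in the text, has two inputs per dimension: one ward's baseline score and the same ward's follow-up score. A conclusion about success is drawn from the difference. Nothing in the text separates a real increase from sampling variation in a ward of a few dozen staff, or from a change that would have happened without the intervention. The comparison wards exist for the second purpose, but this reading does not use them.

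This matters because the first result announced in the abstract is how interventions can be tailored to optimise job resources and recovery opportunities. Interventions are designed ward by ward, so a ward-level statement of success bears directly on that result. A reader who follows the section as written could report that a ward's intervention raised, say, physical recovery when the profile shows only noise or drift.

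**Working it through.** The article states no error rate or threshold for the change-profile, so there is no figure of its own to reproduce. The sample-size calculation concerns emotional exhaustion and plays no part here.

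**Inputs**
- Staff per ward: 150 + 150 = 300 over 8 wards (Overview) gives 37.5, taken as n = 37 before non-response and drop-out.
- SD of a ward member's scale score: not given. Assumed 0.7 points, range 0.5 to 0.9.
- Correlation r between baseline and follow-up scores of the same person: not given. Assumed 0.5, range 0.3 to 0.7.
- Lower responding ward size: assumed 20.

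**1. Increase taken at face value, no true change, no drift.** The change in a ward mean is symmetric about zero, so P(rise) = 0.50. Simulation with discrete 1–5 items (3, 5 or 6 items; 20, 30 or 37 staff) gives 47% to 51%, with exact ties in 1% to 3% of cases.

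**2. Informal tolerance t.** The standard error of a ward's mean change is SE = SD × √(2(1 − r)/n) = 0.7 × √(2 × 0.5/37) = 0.7 × 0.164 = 0.115 points. The chance of a rise above t with no true change is 1 − Φ(t/SE):

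| Tolerance t (points) | t/SE | Chance of a rise above t |
|---|---|---|
| 0.05 | 0.43 | 33% |
| 0.1 | 0.87 | 19% |
| 0.2 | 1.74 | 4% |
| 0.3 | 2.61 | 0.5% |

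Over SD 0.5 to 0.9, r 0.3 to 0.7 and n 20 to 37, the figure for t = 0.1 runs from 6% to 34%.

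**3. Drift.** Suppose all wards rise by an assumed 0.1 points for reasons unrelated to the intervention. A ward then shows a rise with probability Φ(0.1/0.115) = 81%. With a fall of the same size it is 19%. A before-after reading cannot tell drift from effect. Dimensions chosen because they were low at baseline would also tend to rise through regression to the mean, which pushes the rate above one half for exactly the dimensions of interest. The article gives no basis for sizing this.

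**4. What an interval would show for one ward.**
- Ward alone, in SD units: 1.96 × √(2(1 − r)/37). This is 1.96 × 0.164 = 0.32 at r = 0.5 and 1.96 × 0.127 = 0.25 at r = 0.7.
- Net of one paired comparison ward of equal size: multiply by √2. This gives 0.46 at r = 0.5 and 0.35 at r = 0.7.

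So the net change for a single ward pair has a chance range of about ±0.35 to ±0.46 SD. This counts sampling of staff only. Ward-level fluctuation would widen it and cannot be estimated from one ward against one ward.

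**The case against.** The strongest reply is that the profile is a descriptive feedback display. It extends the risk-profile that is discussed with staff, while formal inference comes from the multilevel model, whose wording is not limited to health, well-being and performance outcomes. The outcome sentence also separates the profile from the determination of outcome effects, and nothing says the profile overrides the model. The article condenses a fuller plan, and its example figures are not shown, so intervals may appear elsewhere.

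Much of this stands. The model is planned and can supply the missing inference, and the observation applies to the article's text only. What does not stand is that the text already says so. It appears under a heading about evaluating effects and says that the profile shows success. The contrast with outcome measures leaves the profile as the only criterion which that section gives for resources and recovery.

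Several stronger readings are tempting but unsupported:
- A reader might infer that every rise counts as success, so that the plan has a fixed 50% false-success rate. No cut-off is written, and the example treats near-equal demand scores as unchanged, which implies some unquantified tolerance.
- A reader might multiply the chances over six dimensions or four intervention wards. The article never calls a ward successful because any one of six dimensions rose, nor the programme successful because any one ward did.
- A reader might fear that wards labelled successful will be linked to better outcomes. No such analysis is planned.
- A reader might compare the chance range with the half-SD difference in the sample-size section. That benchmark was set for emotional exhaustion between two groups, not for change within a ward on these scales.

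**Conclusion.** The point holds as a defect in how success is defined. A before-after display for a single ward is said to show success, with no stated criterion for chance, no comparison-ward contrast and no link to the model that could provide both.

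With no true change and no drift, the chance of a rise on a given dimension is about one half if increases are taken at face value. It is about 19% with a tolerance of 0.1 points and 4% with 0.2 points, under SD 0.7, r = 0.5 and 37 staff. With upward drift, or regression to the mean on targeted dimensions, one half is not a ceiling. SD, correlation and responding ward size are assumptions, so the tolerance figures are illustrative. The face-value figure rests only on symmetry. The overall multilevel evaluation is not undermined by this. The risk is confined to statements about resources and recovery that rest on the profiles alone.

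**What to change.** In the section on evaluating the effects of workplace interventions, replace the success reading with wording to this effect:

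> The change-profile is descriptive. For each dimension it shows the ward's change with its 95% confidence interval, beside the change in the paired comparison ward. The dimension or dimensions targeted in each intervention ward are recorded, with a date, before implementation. Whether the interventions increased job resources or recovery is judged from the group-by-time estimate, with its 95% confidence interval, from the multilevel repeated measures model fitted to the resource and recovery scales using all available responses.

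Using all available responses keeps this in line with the Drop-outs and Data-analysis sections, which retain incomplete cases. The Discussion says the baseline survey is done and the interventions are still to be implemented, so the targeted dimensions can still be recorded in time.

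The cost is one paragraph, a dated list, intervals on the profiles and the planned model fitted to six further scales; no new data are needed. There are two downsides. Single-ward changes will often be inconclusive, given a chance range of about ±0.35 to ±0.46 SD for one ward pair before any ward-level fluctuation. And because interventions are tailored by ward, a pooled estimate for a dimension targeted in only some wards will be diluted, so it should be read alongside the recorded list of targets.

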### Process evaluation

It is impossible to control all external influences on performance, well-being and health from the implementation of the interventions until the follow-up measures. However, some actions will be taken to get insight into factors that possibly affect the results. Therefore, a process evaluation will be carried out [42]. The aim of this evaluation is to map factors that either stimulated or hindered successful implementation as well as the effectiveness of the interventions. The managers of the involved wards will be asked to note important changes and events on their wards in a logbook. Both after the first follow-up survey an the second follow-up survey, in-depth interviews will be held with the managers and nursing staff of both the intervention and comparison wards to interpret possibly changes in performance, well-being, and health on their ward. It will also be checked if employees on the intervention wards really perceived interventions. At the last page of both the follow-up surveys, they will be asked to list actions (since the previous survey) that were taken to improve health, well-being and performance on their ward. The same will be done with employees of the comparison wards. Consequently, it can be checked if managers of the comparison wards implemented interventions on their own initiative. In general, we will follow the intervention evaluation criteria as depicted by Scharf et al. [28] as much as possible.

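### The section on evaluating effects judges success by before-after change without the comparison wards, and this is not reconciled with the controlled design or the multilevel analysis

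*Protocol article*

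**What the plan says.** Two statements under Evaluating the effects of workplace interventions fix how success is judged.

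- For outcomes such as physical complaints: "the average score of the first follow-up survey will be compared with the score from the base-line survey".
- For job resources and recovery: "a change-profile will we developed for each ward", holding that ward's baseline and follow-up scores, and "The change-profile shows if an intervention is successful in increasing specific types of job resources and recovery opportunities". The profiles are drawn again after the second follow-up.

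The comparison wards are not mentioned in that section. Elsewhere the article describes a controlled study:

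- Overview calls it a "non-equivalent control group pretest posttest design" and states that "four wards will be the comparison group", with 150 staff in each group.
- Sample size calculation is set up for an experimental group against a comparison group.
- Discussion says that intervention and comparison wards were chosen as similar pairs.
- Data-analysis says: "To evaluate the results of the interventions after the follow-up measures, multilevel repeated measures analysis will be performed using MLwiN". It does not say which term of that model is the intervention effect.

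**The concern.** A comparison group is there so that change which would have happened anyway can be subtracted. A rule that sets follow-up against baseline does not subtract it. Whatever moves all wards between the two surveys, such as season, sector policy or staffing, then counts as intervention effect. The authors expect such influences: "It is impossible to control all external influences on performance, well-being and health from the implementation of the interventions until the follow-up measures". Their answer is the process evaluation, which helps to interpret a change but does not remove drift from an estimate.

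The sentence in Data-analysis does not settle the matter. A repeated measures model can report a time effect or a group-by-time effect, and the sentence is compatible with either. It and the evaluation section do not refer to each other. An analyst or reader who takes the evaluation section at its word could declare success for a change that was just as large on the comparison wards.

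The change-profiles raise a smaller, second issue. Development of workplace interventions takes the baseline risk-profiles as the starting point, and its worked example targets scales that scored low. The same baseline score then serves as the before value. Scales chosen partly because they were low may rise somewhat through regression to the mean.

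**Working it through.** The plan gives no figure for the before-after rule, so there is none to reproduce. The sample size calculation matters here only because it shows a between-group contrast; its size is not used.

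**Inputs from the article.** 150 intervention and 150 comparison staff in four wards each, so 150 / 4 = 37.5, about 38 per ward. Alpha 0.05, taken as two-sided because the article does not say. Relevant difference: half an SD.

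**Assumptions not in the article.** A drift common to all wards of 0.1 to 0.3 SD; a T1-T2 correlation r of 0.3 to 0.7; a paired normal test of T2 minus T1 (the section names no test); all staff answer both surveys; clustering ignored.

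**What each rule estimates.** Let the intervention effect be e and the drift d_I on intervention wards and d_C on comparison wards.

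- Before-after: e + d_I.
- Difference in changes: e + (d_I - d_C), which equals e when the drift is common.

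**Chance of a significant before-after result when e = 0.** In SD units, SE = sqrt(2(1 - r)/n). The rejection probability is Phi(d/SE - 1.96), plus a negligible lower tail. For n = 150 and d = 0.2:

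| r | SE | d/SE | Probability |
|---|---|---|---|
| 0.3 | sqrt(1.4/150) = 0.0966 | 2.07 | 0.544 |
| 0.5 | sqrt(1.0/150) = 0.0816 | 2.45 | 0.688 |
| 0.7 | sqrt(0.6/150) = 0.0632 | 3.16 | 0.885 |

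Other settings, over the same range of r:

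- d = 0.1, n = 150: 0.179 to 0.353.
- d = 0.3, n = 150: 0.874 to 0.997.
- d = 0.2 in one ward of 38: 0.181 to 0.356.

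A drift of 0.2 SD is 0.2 / 0.5 = 40% of the difference that the plan calls relevant.

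**The controlled contrast.** With equal independent groups, SE = sqrt(2) × the before-after SE, a factor of 1.41. At r = 0.3 that is 1.41 × 0.0966 = 0.137. Under common drift and e = 0 it rejects in 5% of cases. Its power for 0.5 SD with 150 per group is 0.955 at r = 0.3, 0.991 at r = 0.5 and above 0.999 at r = 0.7. These powers ignore clustering and drop-out, so they are upper values.

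**Regression to the mean in the profiles.** No figure is given. Its size depends on how targets are chosen. The article describes weighing resources and recovery against demands and then seeking consensus among staff, which is not a rule that can be computed.

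**The case against.** The strongest reply is that the evaluation section is not the inferential plan. It names no test or threshold and mainly explains how the profiles are built and read. Data-analysis assigns evaluation of the interventions to a multilevel model, and the design, sample size and ward pairing all point to a comparison between groups. The process evaluation also covers both groups: "in-depth interviews will be held with the managers and nursing staff of both the intervention and comparison wards". Change-profiles are promised for every ward, so comparison-ward profiles may well exist. And a journal article commonly leaves model terms to a fuller plan.

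Much of this stands. A reader might infer that the whole study is uncontrolled; the documents do not support that. An unnamed group-by-time term would, by itself, be no finding in a condensed article. What remains is a positive statement of how the effect is determined, which leaves out the comparison wards and conflicts with the article's own design. Nothing says which account governs.

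Three further inferences are tempting and are not supported:

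- **Regression to the mean in the outcomes.** Wards joined because they were interested; no selection on extreme outcome scores is stated. The point reaches only the profile scales.
- **Leavers shifting the averages.** The article is silent on whether the averages are restricted to staff with both surveys. It does plan linked identification numbers, attrition analyses and a model that keeps incomplete cases.
- **A ward-by-ward outcome rule.** The ward is the stated unit for the change-profiles. The outcome sentence names no unit.

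**Conclusion.** The point holds as an unreconciled effect rule. The section that says how effects are judged describes a before-after comparison, for outcomes and for the profile scales, and makes no use of the comparison wards. The multilevel analysis does not resolve this, because it names no group contrast and is not linked to that section.

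That the before-after rule absorbs common drift in full follows from the algebra and needs no assumption. The 54% to 88.5% false-positive range is only an illustration: it rests on an assumed 0.2 SD drift, an assumed correlation, a test the section does not name and no clustering, and it applies to the pooled group rather than to one ward. The documents give no estimate of actual drift. For the change-profiles, some regression to the mean is possible, of a size that the article does not allow to be fixed.

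**What to change.** In Evaluating the effects of workplace interventions:

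- Replace the before-after sentence. Define the effect on each outcome and each DISC scale as the T1-to-T2 change on intervention wards minus that on comparison wards, and likewise for T1 to T3. State that it is estimated as the group-by-time term of the multilevel model in Data-analysis, and refer to that section.
- Label the change-profiles as descriptive, remove the statement that they show success, and show the paired comparison ward's baseline and follow-up scores beside each one.

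The cost is a few sentences and one added series per profile; both groups are already surveyed. The statistical price is a standard error about 1.4 times that of the before-after comparison. The contrast removes only drift common to both groups. Wards are not randomized, and in the Northern home the two groups work at different locations, so differential drift can remain. The process evaluation is still needed to interpret it.
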